### PROSOM-K procedure

Following the phase of inclusion, the experiment is divided into three sequential sessions: session 1 (familiarisation), day-time session, and night-time session [see Additional file 2]. The interval between two consecutive sessions is about one week, and the order of day-time and night-time sessions is counterbalanced between participants. During each session, participants will have to learn nine intentions and retrieve them in the virtual environment after a delay of 10 min for session 1, and about 12 h for the two other sessions. The lists of 9 intentions are composed of 3 TB intentions (e.g. at 12:11 ➔ go to the restaurant for the lunch), 3 linked EB intentions, i.e. with a strong link between the prospective cue and retrospective component (e.g. at the cafeteria ➔ buy a black coffee), and 3 no-linked EB intentions (e.g. at the child-care centre ➔ ask for a map of the Memorial).

**Session 1** allows for the familiarisation of participants with virtual reality use and PM task. This session will be performed either at 8:30 or at 18:30 to assess a potential effect of time on learning and PM performances. A guided-visit of the virtual Memorial Museum will be realised to teach participants how to navigate in the virtual environment, display the time and the map with the joystick, and locate every place and component of the environment. The visit will be followed by a phase of learning the intentions, and after a delay of 10 min, participants will go back to the virtual Memorial to retrieve the intentions.

**Day-time session** is divided into two parts. The first part will take place at 8:30, subjects will learn new intentions. The second part will take place at 19:00, during which participants will go into the virtual environment and retrieve the intentions.

**Night-time session** is also divided into two parts. The first part will begin at 17:30, PSG will be placed, and after a meal, women will learn new intentions. Participants will come the next day at 8:30 to have PSG removed, and recall intentions in the virtual Memorial.

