**Retrieval phase**

After an interval of 10 min or 12 h, participants will enter the virtual Memorial for the retrieval phase. Intentions will be retrieved during an ongoing task that requires participants to focus their attention on this task and not on the intentions. The ongoing task consists in visiting the Memorial and going to every location indicated by a yellow rectangle on the map, to observe and memorise photographs that they will have to be recognised after the PM task. Every time participants will be in front of a photograph, the yellow rectangle of the emplacement will disappear from the map. Thus, participants will be able to know what photographs remain to be seen.

For TB intentions, a button on the flystick will allow participants to display the hour on the screen. When at a certain time or place, subjects will retrieve an intention, they will have to say out loud what they are supposed to do. Even if the time is up, or if only prospective or retrospective components are retrieved, women will have to express it. Participants will be immersed for about 15 min in a visit of the Memorial, to view and memorise all photographs and retrieve the intentions.

At the end of the virtual reality task, participants will have to say how many intentions they think they have retrieved, which will allow us to assess their metamemory ability, and a free recall test of all intentions will be realised. For unrecalled intentions, a cued recall test will be done and participants will have to say for EB intentions if they have noticed the prospective component in the environment.

Then participants will realise a recognition task of the photographs seen during the ongoing task. Thirty photographs will be displayed on a laptop screen among which 15 are present in the virtual Memorial. Participants will have to respond “YES” or “NO”. The order of the screening of photograph sets is counterbalanced between day-time and night-time sessions, and the total score will be 30 points. Finally, they will complete a debriefing, noting from 0 to 10 the logic of the link between prospective and retrospective components and the importance for them to realise each intention. Indeed, the importance for the participant to realise an intention will influence her motivation and the processes used to retrieve the intention, and thus the probability of realising the intended action.

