## Discussion

Numerous BC patients survivors report memory troubles. A recurring complaint is that they forget what they are supposed to do at the right moment, referring to PM. This PM is essential for self-sufficiency and medical adherence and thus the well-being of BC patients. Few studies have been published on PM functioning in BC patients, and PM process impairment needs to be more precisely evaluated. Coupled with PM impairment, several BC patients report sleep disturbances. Few studies have used PSG to assess sleep in BC, but results have revealed a decrease of sleep quality in BC patients. Knowing the involvement of sleep in memory consolidation, these results support the necessity to investigate the link between memory impairment and sleep disturbances in BC. Furthermore, HT seems to have a negative impact on memory and sleep, but there is still a lack of research in this area.

The current study will assess PM using an innovating and ecological virtual reality based task. The different types of components and intentions will be distinguished and correlated with performances in various neuropsychological tests. These tests will assess working memory, episodic memory, and executive functions known to be involved in PM functioning. The findings are expected to improve understanding of PM impairment and underlying mechanism in BC patients. Sleep will be assessed by PSG in order to obtain additional information related to sleep architecture. Sleep architecture parameters will also be correlated to PM scores and performances at night-time and day-time sessions will be compared in order to put forward the consolidation of prospective memories during sleep. These various assessments will be performed among BC patients treated or not with HT and healthy women, so that it will be possible to bring to light the possible specific impact of either BC and/or HT on PM functioning and sleep quality.

Even though the current study aims at assessing PM using an ecological task in a virtual environment, it remains a limitation. Virtual reality may provoke uncomfortable sensations like nausea and dizziness. Session of familiarisation will allow participants to become accustomed with virtual reality. If at the end of the session 1, participants are not used to virtual reality and feel sick, the task will be stopped and they will be withdraw from the study.

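### The stated delay of about 12 h does not match the day-time clock times (about 10.5 h), and the night-time delay is probably longer, so delay length may go with sleep in the day-night comparison

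*Protocol article*

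**What the plan says.** Under PROSOM-K procedure, one delay is given for both long-interval sessions: "after a delay of 10 min for session 1, and about 12 h for the two other sessions". The Retrieval phase text repeats it without the qualifier: "After an interval of 10 min or 12 h, participants will enter the virtual Memorial for the retrieval phase".

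The same procedure section then gives clock times. For the day-time session: "The first part will take place at 8:30, subjects will learn new intentions" and "The second part will take place at 19:00, during which participants will go into the virtual environment and retrieve the intentions". For the night-time session: "The first part will begin at 17:30, PSG will be placed, and after a meal, women will learn new intentions", followed by "Participants will come the next day at 8:30 to have PSG removed, and recall intentions in the virtual Memorial". No clock time is attached to night learning.

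The comparison of the two sessions belongs to the first secondary objective (Study objectives). The Discussion says how it will be read: "performances at night-time and day-time sessions will be compared in order to put forward the consolidation of prospective memories during sleep". Session order is counterbalanced between participants. The article states no matching of delay length beyond the common figure of about 12 h.

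**The concern.** A day-night comparison can be credited to sleep only if the two retention intervals are otherwise alike, above all in length. The article's own model is of this kind: the Background cites a study that set a 12 h sleep delay against a 12 h wake delay. Here the day-time clock times do not give the stated figure, and the order of steps on the night-time evening suggests a longer interval.

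If the night delay is longer for nearly every woman, the contrast mixes sleep with retention length. Counterbalancing the order of sessions does not help, because each woman's night session follows the same timetable whether it comes first or second. Running session 1 at 8:30 or 18:30 does not help either, since it examines time of day at a 10 min delay only.

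By general reasoning (the documents give no forgetting rate), a longer night delay allows more forgetting at night. A small or absent day-night difference would then be hard to interpret.

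**Working it through.** **Inputs from the protocol article (PROSOM-K procedure, Retrieval phase)**
- Stated delay: about 12 h, or 12 h, for both sessions.
- Day: learning part at 8:30, retrieval part at 19:00.
- Night: start at 17:30, then PSG placement, meal and learning; next day PSG removal from 8:30, then recall.

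**Not stated, so varied:** *s*, the time for PSG placement plus meal, and *r*, the time for PSG removal before recall. The Sleep assessment section lists twenty EEG electrodes, eye, chin and cardiac electrodes, respiratory belts, thermistors and an oximeter, but no duration.

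**Step 1: reproduce the stated figure for the day.**
Day delay = 19:00 − 8:30 = 10.5 h. The stated 12 h is not reproduced. The shortfall is 12 − 10.5 = 1.5 h, and 1.5/12 = 12.5%. The two times mark the start of each part, so 10.5 h is approximate. If learning starts *a* hours after 8:30 and retrieval *b* hours after 19:00, the delay is 10.5 − *a* + *b*. Reaching 12 h would need *b* − *a* = 1.5 h.

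**Step 2: night delay.**
Night delay = (8:30 next day + *r*) − (17:30 + *s*) = 15 − *s* + *r* hours. With *r* = 0:

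| *s* (h), assumed | Learning starts | Night delay (h) | Night minus day (h) |
|---|---|---|---|
| 1.0 | 18:30 | 14.0 | 3.5 |
| 1.5 | 19:00 | 13.5 | 3.0 |
| 2.0 | 19:30 | 13.0 | 2.5 |
| 2.5 | 20:00 | 12.5 | 2.0 |
| 3.0 | 20:30 | 12.0 | 1.5 |
| 3.5 | 21:00 | 11.5 | 1.0 |
| 4.5 | 22:00 | 10.5 | 0.0 |

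Each half hour of PSG removal before recall adds 0.5 h to the last two columns.

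**Step 3: when are the delays equal?**
15 − *s* + *r* = 10.5 gives *s* = 4.5 + *r*. With *r* = 0, learning would have to start at 22:00, which is 4.5 h after arrival.

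**Step 4: size under the working assumption.**
For *s* between 1.5 and 3 h the night delay is 13.5 to 12 h. The excess over the day is 3 to 1.5 h, that is 3/10.5 = 29% to 1.5/10.5 = 14%.

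**The case against.** **The night figure is not in the documents.** A reader might infer that the clock times themselves show a night delay of 12 to 13.5 h. They do not. The article gives no time for night learning and no duration for placement or meal, so that range rests wholly on the assumed 1.5 to 3 h. This stands. A night delay of about 12 h is quite possible, and the internal conflict that needs no assumption is on the day side only.

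**The day figure is approximate.** A reader might take 10.5 h as a ceiling. Fatigue and sleepiness scales come before learning and before retrieval, the mood scale comes before retrieval, and neuropsychological tests are given during each session. The true interval can shift either way. This stands, but a shift large enough to reach 12 h would need retrieval to slip 1.5 h further than learning.

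**The label says about.** This holds for the procedure section; the Retrieval phase text drops the qualifier. Loose rounding would be harmless if both sessions were off by the same amount, but the order of steps suggests that they are not.

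**Detail may lie elsewhere.** The article refers to an additional file for the session sequence, and the full protocol is not shown. The absence of a night clock time or of time logging is therefore not a fault in itself. The mismatch between the stated delay and the stated day times is one.

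**The bias is conservative and narrow.** A longer night delay would more probably hide a sleep benefit than create one. All three groups follow the same schedule, so group comparisons within a session, including the hormonal therapy comparison, are untouched. The planned correlations of sleep architecture with memory scores do not depend on equal day and night delays. All of this stands and limits the reach of the point.

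**Adjustment afterwards is not excluded.** One might say that delay can never be separated from condition. That is too strong: variation in set-up time and in learning to criterion may produce some overlap in delays. Where there is none, adjustment is extrapolation.

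**Conclusion.** The point holds in a limited form. On the stated day-time clock times the delay is about 10.5 h, not about 12 h; this needs no assumption beyond learning and retrieval starting near the times given. The night delay is longer unless learning starts as late as about 22:00. Under an assumed 1.5 to 3 h for PSG placement and meal, with recall at 8:30, it is longer by 1.5 to 3 h.

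Delay length would then differ systematically between the wake and sleep conditions in a stated secondary contrast, and order counterbalancing would not remove it. The likely direction, against a sleep benefit, is general reasoning, and the effect on scores cannot be sized from the documents. The primary objective and the group comparisons within a session are not affected. The change is worth making because the contrast is to be read as sleep consolidation and the remedy is cheap.

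**What to change.** 1. Reconcile the delay given under PROSOM-K procedure and Retrieval phase with the clock times: set one common learning-to-retrieval interval and schedule learning and retrieval in both sessions to meet it. This includes a set time for night learning.
2. Record the actual end of learning and start of retrieval for every woman in both sessions, and report the delays by session and group.
3. Use the recorded delays in a sensitivity analysis of the day-night contrast over the range where day and night delays overlap, and say so if they do not overlap.

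The cost is moving one appointment by an hour or two and logging two times per session. If sessions have already been run, correct the stated delay, report whatever actual delays can be recovered, and state that the day-night difference may partly reflect unequal retention intervals.

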### PM task

**Learning phase**

The PM task will begin with a phase of intentions learning. Each intention will be displayed during 10 s on a laptop screen and participants will have to read each of them out loud. Following every three intentions, a cued recall test of these intentions will be realised (e.g. “What will you have to do at 12:11?”). Any unrecalled intentions will be repeated once. After the presentation of all intentions, a cued-recall test will be realised and unrecalled or incorrectly recalled intentions will be repeated. This operation will be done with all unrecalled intentions, until all of them are correctly encoded. Finally, to ensure that all intentions are correctly encoded, they will be retrieved in a last global cued recall test. At the end of this learning phase, participants will have to say how many intentions they think they will remember during the virtual reality task in order to assess their metamnesic awareness.

**Retrieval phase**

After an interval of 10 min or 12 h, participants will enter the virtual Memorial for the retrieval phase. Intentions will be retrieved during an ongoing task that requires participants to focus their attention on this task and not on the intentions. The ongoing task consists in visiting the Memorial and going to every location indicated by a yellow rectangle on the map, to observe and memorise photographs that they will have to be recognised after the PM task. Every time participants will be in front of a photograph, the yellow rectangle of the emplacement will disappear from the map. Thus, participants will be able to know what photographs remain to be seen.

For TB intentions, a button on the flystick will allow participants to display the hour on the screen. When at a certain time or place, subjects will retrieve an intention, they will have to say out loud what they are supposed to do. Even if the time is up, or if only prospective or retrospective components are retrieved, women will have to express it. Participants will be immersed for about 15 min in a visit of the Memorial, to view and memorise all photographs and retrieve the intentions.

At the end of the virtual reality task, participants will have to say how many intentions they think they have retrieved, which will allow us to assess their metamemory ability, and a free recall test of all intentions will be realised. For unrecalled intentions, a cued recall test will be done and participants will have to say for EB intentions if they have noticed the prospective component in the environment.

Then participants will realise a recognition task of the photographs seen during the ongoing task. Thirty photographs will be displayed on a laptop screen among which 15 are present in the virtual Memorial. Participants will have to respond “YES” or “NO”. The order of the screening of photograph sets is counterbalanced between day-time and night-time sessions, and the total score will be 30 points. Finally, they will complete a debriefing, noting from 0 to 10 the logic of the link between prospective and retrospective components and the importance for them to realise each intention. Indeed, the importance for the participant to realise an intention will influence her motivation and the processes used to retrieve the intention, and thus the probability of realising the intended action.

### Outcome measures

#### PM task

During the learning of each of the 9 intentions (3 per type of intention, i.e. 3 linked EB, 3 no-linked EB, and 3 TB), a score [0–1] will be attributed per intention for the first cued recall (see Table 2). We will also evaluate the number of repetitions needed to correctly recall all intentions. The maximum total PM encoding score of each session will be 9 points, corresponding to the sum of the points attributed for each intention (1point * 9 intentions).

During the retrieval of the 9 intentions, a score [0–6] will be attributed for each intention corresponding to the points allocated for the prospective component [0–2], the retrospective component [0–2], and the associative component (i.e., the simultaneous retrieval of prospective and retrospective components) [0–2] (see Table 2). The maximum total PM retrieval score of each session will be 54 points, corresponding to the sum of the maximal scores attributed for each intention (6 points * 9 intentions).

**Table 2 Tab2:** Scoring of each intention of the PM task

LEARNING SCORE [range]			
1 point	Intention is correctly recalled during the immediate cued recall [0–1]		
RETRIEVAL SCORES [range]			
	Prospective [0–2]	Retrospective [0–2]	Associative [0–2]
2 points	Action realised at the first passage in front of the cue or at the right time	Retrospective component is complete	Prospective and retrospective components are recalled together
1 point	Action realised at the second passage or at +/− 1 min	Retrospective component is incomplete (one element is incorrect or forgotten)	–
0.5 point	Action is realised at a subsequent passage or at +/− 2 min	–	–
0 point	Action is not realised	Retrospective component is not retrieved	Prospective and retrospective components are not recalled together

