## Background

Breast cancer (BC) is the most frequent cancer in women and its incidence is increasing [1]. Among these patients, some of them experience cognitive troubles and especially difficulties remembering what there are supposed to do at the right time or in the right place [2, 3]. These memory lapses concern prospective memory (PM) which refers to our ability to remember to accomplish intended tasks or actions at some predefined point in the future.

PM is divided into two components: prospective and retrospective. The first of these refers to the process of remembering that something has to be done at the appropriate time or event, while the second refers to the memory of what has to be done (action). Prospective component gathers two types of intentions: Time-Based (TB) intention referring to self-initiated retrieval of the action after a period of time has elapsed or at a certain time; and Event-Based (EB) intention when an event occurs and triggers the remembering of the action. Intention retrieval relies on two types of processes used in a Dynamic Multiprocess Framework: monitoring and spontaneous retrieval. Their use depends on various factors, for example, characteristics of intentions and ongoing tasks, and importance of realising the action. Monitoring refers to keeping an intention in mind while searching for the prospective component. Spontaneous associative retrieval process relies on automatic processes that bring a retrospective component into mind when a prospective component appears [4]. PM functioning involves various cognitive functions, such as episodic memory, executive functions, and working memory. Retrospective episodic memory is required for the encoding, retention and recall of the intention [5]. Executive functions are involved in planning the intention, inhibiting the ongoing task, and switching to realise the intended action. Working memory is required to keep the intention in mind between the recall and the realisation of the action, and the binding process induces a link between prospective and retrospective components creating a unitary representation of the intention in working memory [6]. PM is essential for daily living tasks and, in BC patients, PM is even more essential for medical adherence, autonomy, and return to social and professional life.

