## Methods

### Study objectives

The primary objective of the PROSOM-K study is to assess PM performances in BC patients, in order to determine which components (prospective or retrospective), and types of intentions (EB or TB) are the most impaired in BC patients, and specify which cognitive processes (episodic memory, working memory, or executive functions) are particularly involved in PM decline in BC patients.

The secondary objectives are to:clarify the influence of sleep disturbances in BC on PM deficits, using various sleep quality assessments (polysomnography, actigraphy and self-report questionnaires), and by comparing PM scores in two different conditions, depending on the type of delay between encoding and retrieval of intentions: day-time and night-timeassess the influence of HT on PM functioning by comparing PM scores between BC patients treated with HT and BC patients not treated with HT.

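### An intention that never comes to mind during the virtual visit scores 0 on the retrospective as well as the prospective component, so a purely prospective deficit can show up partly as a retrospective one

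*Protocol article*

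**What the plan says.** **Objective.** The protocol article (Study objectives) sets out to assess prospective memory "in order to determine which components (prospective or retrospective), and types of intentions (EB or TB) are the most impaired in BC patients". The Background defines the two components separately: remembering that something is due, and remembering what it is. It also criticises earlier studies for not telling them apart.

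**Scoring.** Outcome measures, PM task, states: "During the retrieval of the 9 intentions, a score [0–6] will be attributed for each intention". Each intention earns up to 2 points for each of three components, and Table 2 gives the anchors. The zero anchors are:
- prospective: "Action is not realised"
- retrospective: "Retrospective component is not retrieved"
- associative: "Prospective and retrospective components are not recalled together"

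Partial prospective credit (1 or 0.5 point) is given for later passages or small timing errors. The session maximum is 54.

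**What the woman may say.** Under Retrieval phase, she is asked to speak up during the visit even if she is late or has only one of the two components.

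**What is collected afterwards.** Once the visit ends there is a free recall of all intentions. Then: "For unrecalled intentions, a cued recall test will be done". For event-based intentions she is also asked whether she noticed the cue. The article attaches no points to these answers in Table 2, Table 3 or the 54-point total. The photograph recognition in the same section is scored out of 30.

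**The concern.** Take a woman who passes the cafeteria without remembering that anything is due there. She says nothing and scores 0 prospective, 0 retrospective and 0 associative. She gets the same scores whether she has forgotten the action or would name it at once if cued. Every intention is learned to criterion beforehand (Learning phase), so failing to think of an intention that is still known is a realistic kind of miss.

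The in-task retrospective score therefore depends partly on prospective success. If patients differ from controls only in detecting cues or times, their retrospective score will tend to be lower too. The article could then report impairment of both components when only one is impaired, on the distinction that it presents as its advance over earlier work.

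**Working it through.** **1. The plan's own figure.** (2 + 2 + 2) points × 9 intentions = 54, as stated. Each component has a maximum of 2 × 9 = 18. The three components use up the whole 54, so none of it comes from a separate post-task recall score.

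**2. Inputs for the illustration.** None of these is in the article; all are assumed.
- p: chance that an intention comes to mind in the visit, 0.80 in controls and 0.60 in patients.
- r: chance that the action is still known, equal in both groups, so the true retrospective gap is 0. Central value 0.95, range 0.90 to 1.00.
- f: chance that the content of a missed intention is voiced in the visit anyway, without prospective credit.

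**3. Upper end: all-or-none detection, nothing voiced after a miss (f = 0).**
- Prospective gap: 18 × (0.80 − 0.60) = 3.60.
- Retrospective gap: 18 × 0.95 × (0.80 − 0.60) = 3.42.
- Carry-over: 3.42 / 3.60 = 95%.

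**4. Effect of voicing content without the cue.** Expected in-task retrospective score = 18 × r × [p + (1 − p) × f], so the spurious gap = 18 × r × 0.20 × (1 − f).

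| r | f = 0 | f = 0.25 | f = 0.5 | f = 1 |
|---|---|---|---|---|
| 0.90 | 3.24 | 2.43 | 1.62 | 0 |
| 0.95 | 3.42 | 2.57 | 1.71 | 0 |
| 1.00 | 3.60 | 2.70 | 1.80 | 0 |

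**5. Effect of graded late credit.** Suppose half of the extra 20% of misses are recovered at the second passage (prospective 1 point, retrospective content intact), with r = 0.95.
- Prospective gap: 9 × (0.10 × 1 + 0.10 × 2) = 2.70.
- Retrospective gap: 9 × 0.10 × 2 × 0.95 = 1.71.
- Carry-over: 1.71 / 2.70 = 63%.

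If all are recovered, the prospective gap is 9 × 0.20 × 1 = 1.80 and the retrospective gap is 0.

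**6. Would it reach significance?** Simulation with 25 women per group, two-sided t-test at 0.05, 2,000 runs, r = 0.90, between-woman SD 0.8 on the logit scale (assumed) and no graded late credit. The table gives the share of trials with a significant retrospective difference although none exists.

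| p, controls vs patients | in-task, f = 0 | f = 0.25 | f = 0.5 | post-task recall |
|---|---|---|---|---|
| 0.80 vs 0.60 | 79% | 66% | 46% | 4–5% |
| 0.80 vs 0.70 | 33% | 24% | 15% | 4–5% |

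The post-task column assumes that post-task recall measures action memory without error.

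**The case against.** **The occasion of scoring is not stated for this column.** Only the prospective anchors refer to passages and times. The retrospective anchors name no occasion, and the post-visit recall stands under the heading Retrieval phase. Table 2 could be stretched to include it. This stands as a caution. Even so, the 0–6 score combines retrospective content with visit timing and with the two components being recalled together, which makes in-task scoring the natural reading. If post-task recall was meant to count, the table should say so.

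**The article is condensed.** A reader might infer that the separating data go unused. The documents do not support that: the full protocol or analysis plan may code them. The point rests on the scoring rule that is stated, not on that silence.

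**The carry-over is limited.** A reader might infer that 90–100% of any prospective deficit passes into the retrospective score. That holds only with no late recovery and no voicing without the cue, and the article provides for both. This objection stands, so the figures in step 3 are an upper end.

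**The objective is not lost.** A reader might infer that the component question cannot be answered. It can: free and cued recall are collected from the participants, and episodic memory is also tested independently with the RL/RI-16.

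**The total.** One missed intention costs 6 of the 54 points, but that composite is openly defined and is not what the component comparison uses. No fault is found there.

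**Conclusion.** The point holds in a limited form. On the natural reading of Table 2, an intention never thought of in the visit lowers the retrospective score as well as the prospective one, even when the action is still known. A purely prospective deficit can then appear partly as a retrospective one.

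Under the assumed 80% versus 60% detection and equal 95% action memory, the spurious gap is at most about 3.4 of 18 points. It is 1.71 if half of the extra misses are recovered at the second passage or, separately, if half of the missed content is voiced anyway. It reaches 0 if all are. The article does not allow a choice among these values. The false-positive shares in step 6 rest on the same assumptions plus an assumed spread between women.

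The comparisons of event-based with time-based intentions and the links to other cognitive functions are outside this point. It is worth correcting before the groups are compared, and the data needed are already being gathered.

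**What to change.** For the prospective-versus-retrospective comparison, define the retrospective component [0–2] for all nine intentions as follows:
- **Voiced in the visit:** keep the Table 2 in-task score, including for incomplete, wrong or absent content. Taking the better of in-task and later recall would erase real content errors made in the visit.
- **Not voiced at all:** score the post-task free recall, then the cued recall, with the same complete/incomplete anchors.

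Report the purely in-task score alongside. Where the cue-noticing answer was collected, use it to classify event-based misses.

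**Cost.** A change to the outcome definition and scoring sheet, with no new procedure for participants.

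**Downsides.**
- Cued recall is easier than spontaneous report, and exposure during the visit may help it, so the score may sit nearer its ceiling. At 95% action memory the expected value is 18 × 0.95 = 17.1 of 18 in both groups.
- If content is recalled better afterwards than in the visit, the group with more misses gains slightly. With 90% in the visit and 100% afterwards (assumed, nothing voiced after a miss), the gap is 18 × 0.20 × (0.90 − 1.00) = −0.36 points, in the patients' favour. This is one reason to show both scores.
- The cue-noticing answer does not cover time-based intentions.
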